#### Patient and illness characteristics

In order to examine which patients are most likely to benefit from the intervention, we will assess various potential effect modifiers. The choice of these factors was based in part on the Dutch multidisciplinary guideline for MUPS and somatoform disorders which advocates the use of three patient profiles: mild, moderate and severe symptom profile [36]. Severity depends on factors such as duration, severity and number of symptoms and comorbidity. The potential effect modifiers selected in this study are:Demographic factors: age, gender and education (self-report)Illness duration (self-report)Severity of somatization (somatization scale of the PHQ-15 [27])Physical comorbidity (self-report)Psychiatric comorbidity: anxiety and depression (HADS [43])

#### Potential mediators

The intervention is expected to have positive effects on physical functioning and quality of life through developing problem-solving skills and increasing adequate coping. Moreover, health anxiety and dysfunctional somatic causal attributions are thought to be important aggravating factors of somatoform disorders which are reflected in the new DSM-5 criteria for somatic symptom disorder (formerly somatoform disorders) [44]. Therefore, the following factors will be assessed as potential mediators:Problem-solving skills (Social Problem-solving Inventory [45])Health anxiety (Whiteley Index [46])Illness perceptions (brief IPQ [47])Coping and beliefs about symptoms (CBRQ [48])Mastery (Pearlin Mastery Scale [49])Working alliance (WAI-SF [50])

The Social Problem-solving Inventory Revised: Short Form (SPSI-R:S) measures an individual’s problem-solving strengths and weaknesses. It assesses five dimensions: positive problem orientation, rational problem solving, negative problem orientation, impulsive/careless style and avoidance style. It consists of 25 items that can each be scored on a 5-point Likert scale (0 = ‘not at all true for me’ to 4 = ‘extremely true for me’). Higher scores indicate greater effective social problem-solving skills [45].

The Whiteley Index is a short instrument measuring health anxiety and is often used in investigating symptoms of hypochondria. It consists of 14 items with two answer categories ‘yes’ and ‘no’. A higher score indicates greater health anxiety [46].

The brief Illness Perception Questionnaire (IPQ) is based on the widely used IPQ-R. It is designed in order to rapidly assess the cognitive and emotional representations of illness. It comprises nine items in total. Five items assess cognitive illness representations: consequences, timeline, personal control, treatment control and identity. Two items assess emotional representations: concern and emotions. One item assesses illness comprehensibility. The last item is an open-ended question assessing causal representation [47].

The Cognitive and Behavioural Responses Questionnaire (CBRQ) measures patients’ cognitive and behavioural responses to their illness. This tool has been developed to measure specific cognitions and coping styles in patients with physical symptoms. It consists of 41 items that can be rated on a 5-point Likert scale ranging from ‘strongly disagree’ to ‘strongly agree’. These items add up to four cognitive subscales: catastrophising, damaging beliefs, embarrassment avoidance and symptom focussing; and two behavioural subscales: all-or-nothing behaviour and avoidance/resting behaviour [48].

The Pearlin Mastery Scale measures the level of perceived control, or mastery, over situations in one’s life. It comprises seven items that are scored on a 5-point Likert scale, ranging from ‘completely disagree’ to ‘completely agree’ [49].

The Working Alliance Inventory-Short Form (WAI-SF) is a shortened version of the Working Alliance Inventory (WAI). It is used to measure the therapeutic alliance in an ongoing client-therapist interaction. It comprises 12 items that are scored on a 5-point Likert scale, ranging from ‘never or rarely’ to ‘very often’ [50].

### Factors influencing implementation

#### Non-response and patient satisfaction

Patients who do not want to participate in the study will be asked for reasons for non-participation. Participating patients will receive questions about satisfaction with the content and relevance of the treatment at the 4-month follow-up. The questions will cover topics such as: patients’ expectations and needs prior to treatment; whether the treatment lived up to their expectations; whether patients considered themselves to be the target audience (suffering from USD); patients’ reasons for participating; whether the treatment helped in the short and the long term; satisfaction with the duration of the treatment and whether they would recommend the treatment to someone else in the future. The above questions will be assessed using a 5-point Likert scale ranging from 1 = ‘very satisfied’ to 5 = ‘very unsatisfied’. Also, reasons for dropout will be assessed.

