## Methods/design

This protocol was developed in accordance with the Standard Protocol Items: Recommendations for Interventional Trials (SPIRIT) Statement. For the SPIRIT Figure see Additional file 1 and for the SPIRIT Checklist see Additional file 2. We will conduct a parallel-group, multicentre, cluster randomised controlled trial in 39 primary care centres (a list of the participating centres is provided in Additional file 3). Cluster randomisation will take place at the MHNP and general practice level in order to avoid contamination between the intervention and control conditions. Clusters will be composed by matching MHNPs to all participating general practices where the MHNP works and to all other MHNPs who also work in these general practices. The entire cluster consisting of one or more MHNPs and general practices will then be randomly assigned to the intervention or to care as usual (CAU) group, prior to the inclusion of patients. An independent statistician, not involved in the selection of the practices and MHNPs, will carry out the randomisation. In order to balance the size of the intervention and CAU groups, randomisation will be stratified according to cluster size (small: less than 5000 patients, and large: 5000 patients or more). Assessments will take place at baseline (T0), during the intervention period at approximately 2 months (T1), directly after the intervention period at 4 months (T2), at 8 months (T3) and at 12 months (T4) after baseline.

This study is registered at the Dutch Trial Registry (NTR4686) and was approved by the VU Medical Center Ethics Committee. It will be conducted according to the principles of the Declaration of Helsinki (version 2013). Important protocol modifications will be communicated with the Dutch Trial Registry and the VU Medical Center Ethics Committee.

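### Patients are asked about long-term benefit only at the 4-month follow-up, right after the intervention period, and the single satisfaction scale does not fit several of the listed topics

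*Protocol article*

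**What the plan says.** The section on non-response and patient satisfaction fixes the timing: "Participating patients will receive questions about satisfaction with the content and relevance of the treatment at the 4-month follow-up". It names no other administration. Its list of topics opens with "The questions will cover topics such as" and includes:

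- "patients’ expectations and needs prior to treatment", and whether those expectations were met;
- whether patients saw themselves as the intended group, and why they took part;
- "whether the treatment helped in the short and the long term";
- satisfaction with the length of treatment, and whether they would recommend it.

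One response format is then given for all of these: "The above questions will be assessed using a 5-point Likert scale ranging from 1 = ‘very satisfied’ to 5 = ‘very unsatisfied".

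The Methods/design section sets the later assessments "directly after the intervention period at 4 months (T2), at 8 months (T3) and at 12 months (T4) after baseline". The 12-month contact is therefore already in the schedule. The paragraph on factors influencing implementation, in the statistical analyses, lists satisfaction with the intervention among the data to be obtained.

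**The concern.** Two features of the questionnaire do not match its purpose.

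1. **Timing.** A question about long-term help is put at the moment the intervention period closes. The patient has had no time to observe a long-term result, so the answer is an expectation, yet it would be reported as a rating of benefit. Short-term and long-term answers given at one sitting are also likely to move together, so the distinction that the authors wanted would be lost.

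2. **Response anchors.** A satisfaction scale suits questions about satisfaction. It gives no interpretable answer to why someone joined, or to whether someone regards themselves as a patient with the target disorder. It is awkward for whether treatment helped.

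At stake is the patients' own part of the implementation results. In this document it is the one place where patients are asked directly whether the treatment helped.

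**Working it through.** The plan gives no figure on this point, so the check sets the passages side by side and adds simple date arithmetic.

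**Inputs from the protocol article**
- Questionnaire given at month 4 (Non-response and patient satisfaction).
- Month 4 falls directly after the intervention period, and the last assessment is at month 12 (Methods/design).
- Six sessions of 30 minutes, with no interval between sessions stated (The intervention).
- 106 patients planned per condition, with 20% dropout assumed (Power calculation/sample size calculation).

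**Step 1: experience available when the question is asked.**
If treatment runs to the end of the intervention period, post-treatment experience at the questionnaire is 4 − 4 = 0 months. Because the session interval is not stated, some patients may finish sooner. Treatment cannot start before baseline, so 4 − 0 = 4 months is an upper limit that no patient can reach. The range is 0 to under 4 months, and 0 is the value implied by the article's description of the 4-month assessment.

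**Step 2: experience available if the question is asked at 12 months.**
12 − 4 = 8 months after the intervention period, and somewhat more for anyone who finished early.

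**Step 3: respondents.**
Up to 106 intervention patients could answer at month 4. If the assumed 20% dropout had all occurred by month 12, then 106 × (1 − 0.20) = 84.8, or about 85, would remain to answer there.

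**Step 4: topics against timing and scale.**

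| Topic | Can it be judged at month 4? | Do the satisfaction anchors fit? |
|---|---|---|
| Short-term help | Yes | Loosely |
| Long-term help | No, forecast only | Loosely |
| Satisfaction with duration | Yes | Yes |
| Expectations met | Yes | Loosely |
| Expectations and needs beforehand | By recall | No |
| Belonging to the target group | Yes | No |
| Reasons for participating | Yes | No |
| Would recommend | Yes | No |

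The timing problem is confined to one topic. The scale problem affects several.

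**The case against.** The strongest reply is that the article gives example topics and not the items. The questionnaire is not shown, and a condensed article need not reproduce it. The long-term item may be worded as an expectation, and reasons for participating may be collected in another format. This has force and limits how far the anchor point can be pressed. It does not remove it: the article names the topics and then states one scale for all of them. Nor does it touch the timing, which the article fixes.

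A second reply is that the stakes are low. That is correct. The answers feed no primary or secondary outcome and no mediation or cost-effectiveness analysis. Barriers and facilitators come from interviews with the nurse practitioners.

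A reader might go further and infer three things that the documents do not support.

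- **That worsening after treatment is never recorded.** Table 2 schedules the RAND-36, PHQ-15 and HADS at 12 months and the EQ-5D-5L at 8 and 12 months. All are self-reported and can move in either direction. The questionnaire scale also has a negative end. At most, it cannot separate no benefit from worsening that the patient attributes to the treatment, and no listed topic asks about that.
- **That the treatment rationale itself predicts late harm.** The account of survival strategies that become harmful later concerns strategies patients developed in response to their symptoms. The treatment aims to replace these with more helpful ones.
- **That the questionnaire as a whole fails.** Short-term help, duration, whether expectations were met and willingness to recommend can all be judged at 4 months. Asking about earlier expectations afterwards gives a weaker measure, open to recall, but it is not an error.

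**Conclusion.** The point holds in a narrow form and is minor. As the article stands, long-term help is asked about only when the intervention period has just ended, so the answer is a forecast. Asking at 12 months would replace about 0 months of post-treatment experience with about 8. The satisfaction anchors stated for every question do not suit topics such as reasons for participating or membership of the target group.

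The conclusion rests on two assumptions: that the 4-month administration is the only one, since none other is named, and that the stated scale does apply to all the listed topics. If the actual questionnaire uses other formats for some items, the second part reduces to a correction of the article's text. In either case only the descriptive implementation results are affected. The comparison between groups, including its 12-month measurements, is not.

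**What to change.** - Keep short-term help, satisfaction and duration at the 4-month assessment.
- Ask the long-term question at the scheduled 12-month assessment, or repeat it there. If it also stays at 4 months, label that answer as an expectation.
- State which items use the very satisfied to very unsatisfied anchors and limit them to items about satisfaction. Use agree/disagree answers for target group and recommendation, and a categorical answer for reasons for participating.

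The cost is a few more items in a questionnaire that patients already receive at 12 months, and fewer respondents by then: about 85 of 106 intervention patients under the plan's own dropout assumption. Recruitment was still under way when the article was submitted, so the 12-month item could still be added for patients who had not yet reached that assessment. For anyone already past it, the 4-month answer should be reported as a forecast.

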#### Evaluation MHNPs

The MHNPs in the intervention group will receive a questionnaire to evaluate their opinion about the content and relevance of the treatment. The questions will cover topics such as whether MHNPs felt the treatment was effective for the patients; whether the intervention protocol was useful to the MHNPs and whether they followed the protocol as they were asked to do. Potential reasons for non-compliance will be explored. The questions on the opinions of the MHNPs will also be assessed on a 5-point Likert scale. Additionally, MHNPs will be interviewed by telephone or in person to gain insight into factors that they deem relevant for successful implementation of the intervention in the future and what possible barriers they identify. The interviews will be recorded and transcribed for analysis.

### Handling and storage of data and documents

Data will be collected and stored digitally using the web database NetQuestionnaires. This database treats data with strict confidence and does not disclose data to any third parties without permission of the user. NetQuestionnaires also takes safety measures for collecting, storing and processing data to prevent unauthorised access. In case people prefer a paper version of the questionnaires, this will be sent by regular mail. The completed paper questionnaires will be stored in a locked closet at the Department of General Practice and Elderly Care Medicine. When working with data, subjects will be assigned with a code. The code list will be safeguarded by the principal investigator. Only the principal investigator and research assistants will be able to access the source data. Data will be kept for 15 years.

### Power calculation/sample size calculation

We based the sample size calculation on an expected increase in the primary clinical outcome PCS of the RAND-36 during the total follow-up period (4 and 12 months after baseline). Based on previous findings, we aim to detect a clinically relevant effect size of 0.4. This effect size was previously shown to be feasible in a similar population [18]. The clinically relevant difference on the PCS ranges from 3 to 5 points [51]. Based on an estimate of the standard deviation of the PCS score of 10 [52], our effect size corresponds to a 4-point difference between the intervention group and the CAU group. We assume a two-sided significance level of 5% and a power of 80%. The ratio of the number of subjects in the compared groups is 1:1 and there are two measurements of follow-up for our primary outcome. Although we assume that the results will be similar on both repeated measurements, we opted for a more conservative correlation coefficient of 0.5. Using linear mixed models with these values leads to a sample size of *n* = 74 patients per condition.

However, since our study is a cluster randomised controlled trial, we applied an additional correction for the ‘design effect’ [53] with an expected average cluster size of four. As previous research found that 90% of intra-class correlation coefficients (ICCs) in primary care research are smaller than 0.055 [54], we chose an ICC of 0.05. After applying the correction, the sample size resulted in *n* = 85 patients (1.15 × 74) per condition. Taking a potential dropout rate of 20% into account, we aim to include 106 (85/0.8) patients in each condition.

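### The follow-up correlation of 0.5 is called conservative, but on the natural reading of the sample size calculation it is the favourable choice

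*Protocol article*

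**What the plan says.** The Power calculation/sample size calculation section of the protocol article sets the target as "we aim to detect a clinically relevant effect size of 0.4" and translates it to points: "Based on an estimate of the standard deviation of the PCS score of 10 [52], our effect size corresponds to a 4-point difference". Significance is 5% two-sided and power 80%. On design it says "The ratio of the number of subjects in the compared groups is 1:1 and there are two measurements of follow-up for our primary outcome", and it places these follow-ups at 4 and 12 months. The next sentence introduces the only correlation in the section: "Although we assume that the results will be similar on both repeated measurements, we opted for a more conservative correlation coefficient of 0.5". The result is then given: "Using linear mixed models with these values leads to a sample size of" 74 per condition. No correlation between baseline and follow-up is listed.

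The section then applies a design effect of 1.15 (ICC 0.05, "with an expected average cluster size of four") to reach 85 per condition, and allows for 20% dropout to reach 106.

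Under Statistical analyses, Primary outcomes, the planned analysis is a linear mixed model for differences in change scores on the PCS. Table 2 includes a baseline PCS.

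**The concern.** Calling an input conservative tells the reader that the sample size errs on the safe side if the input is wrong. When a treatment effect is averaged over repeated follow-ups, the direction is the other way. Two highly correlated follow-ups carry little more information than one, so a higher correlation needs more patients. The authors expect similar results at both follow-ups, which suggests a high correlation, and then use a lower one. If their expectation is right, the calculation as described gives less than 80% power, while the text suggests it gives more. This is the power basis for the primary clinical outcome, so the stated direction should be correct.

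**Working it through.** **Inputs**, all from the sample size section: difference 4, SD 10 (d = 0.4), two-sided alpha 0.05, power 80%, allocation 1:1, T = 2 follow-ups, rho = 0.5, design effect 1 + (4 − 1) × 0.05 = 1.15, dropout 20%.

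**Reproducing 74.** For a comparison of the mean of T follow-ups without baseline,

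n per arm = 2(z₀.₉₇₅ + z₀.₈₀)² × [1 + (T − 1)rho] / (T d²)

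= 2 × (1.96 + 0.8416)² × 1.5 / (2 × 0.16) = 73.6, rounded up to 74. Then 74 × 1.15 = 85.1 (stated 85) and 85/0.8 = 106.25 (stated 106). All three figures match.

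**Direction.** For T = 2 the variance factor is (1 + rho)/2, which rises with rho. Correlations other than 0.5 are my assumptions; the document gives none. Power uses the planned 85 analysed per arm, an effective 85/1.15 = 73.9, and power = Φ(0.4/√(2 × factor/73.9) − 1.96).

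| rho between follow-ups | n per arm before clustering | Power at 85 per arm |
|---|---|---|
| 0.5 | 74 | 80% |
| 0.6 | 79 | 78% |
| 0.7 | 84 | 75% |
| 0.8 | 89 | 73% |
| 1.0 (limit: one follow-up) | 99 | 68% |

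The last row is a mathematical bound, not a plausible value.

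**A second formula that also gives 74.** Take the change from baseline to the follow-up mean, with one common correlation among all three time points. The factor is (1 + rho)/2 + 1 − 2rho = 1.5(1 − rho), which is 0.75 at rho = 0.5, hence 74 again. Here n falls as rho rises (45 at 0.7, 30 at 0.8), so 0.5 would be cautious. If instead the baseline correlation stays at 0.5 and only the follow-up correlation rises, the change-score factor is (1 + rho)/2 + 1 − 2 × 0.5 = (1 + rho)/2. The required n is then 84 at 0.7 and 89 at 0.8, as in the table.

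**What baseline adjustment does.** With baseline correlation r_b to each follow-up, the factor becomes (1 + rho)/2 − r_b². At the same effective 73.9 per arm:

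- all correlations 0.5: factor 0.75 − 0.25 = 0.50, power 93%
- all correlations 0.7: factor 0.85 − 0.49 = 0.36, power 98%
- r_b = 0.5, rho = 0.8: factor 0.90 − 0.25 = 0.65, power 85.5%
- unadjusted change score, r_b = 0.5, rho = 0.8: factor 0.90, power about 73%

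The adjusted factor is no larger than the planned 0.75 when r_b² ≥ (rho − 0.5)/2. At rho = 0.8 this means r_b of at least √0.15 = 0.39.

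**The case against.** The strongest reply is that the formula is inferred. The section says only that linear mixed models were used with the listed values, and the common-correlation change-score formula gives 74 just as exactly, with 0.5 then on the cautious side. Matching 74 cannot separate the two. There is also text in favour of change: the section opens with an expected increase in the PCS, the outcome is defined as improvement, and the analysis compares change scores. Quoting the SD of the PCS score does not settle it, because a change-score calculation also starts from the raw SD.

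This lowers certainty but does not remove the point. The correlation is attached to the two repeated measurements, directly after the two follow-ups are counted, and no baseline correlation appears. The post-treatment reading is the natural one. If the change-score version was meant, the section describes a different correlation from the one that makes 0.5 cautious, and still needs correcting.

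Two further objections stand. The protocol does not quantify similarity, and the word could also mean a similar group difference at both times, so every value above 0.5 is illustrative. And the 75% and 73% figures ignore baseline, whereas the planned analysis uses change. A reader might infer from them that the trial is underpowered or must recruit more. The document does not support that inference.

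**Conclusion.** On the natural reading, which reproduces every stated sample size figure, the label *more conservative* has the wrong direction and the safety margin it implies is absent. Under that calculation, power would be about 75% at an assumed follow-up correlation of 0.7 and about 73% at 0.8, instead of 80%.

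The actual power depends on how baseline enters the analysis and on a baseline correlation that the document does not give. In the adjusted cases worked above it exceeds 80%. For an unadjusted change score it is higher than planned if all correlations rise together, and about 73% if the follow-up correlation is 0.8 while the baseline correlation stays at 0.5. So the power statement needs correcting, but a shortfall in the trial is not shown. The point is of moderate weight, and confidence is limited by the formula not being stated.

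**What to change.** In the sample size section:

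1. Delete *more conservative*.
2. State which correlation 0.5 is (between the 4- and 12-month PCS, or a common value that includes baseline) and whether baseline enters the calculation.
3. If it is the correlation between follow-ups, say that higher values lower power in this calculation.
4. Restate power for follow-up correlations of 0.5 to 0.8, labelled as assumptions, under the analysis actually used. Give the assumed baseline correlation alongside.
5. Preferably make that analysis baseline-adjusted rather than an unadjusted change score, since the unadjusted version leaves power exposed when the follow-up correlation exceeds the baseline one.

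The cost is rewording and a short power table. Enrolment stays at 106 per condition, and no extra measurement is needed because Table 2 already has a baseline PCS.
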